**ASSESSMENTS:**																								
**Implant survival** **rate**								X								X								X
**Peri-implant plaque index**				X		X		X		X		X		X		X		X		X		X		X
**Bleeding on probing**				X		X		X		X		X		X		X		X		X		X		X
**Suppuration**				X		X		X		X		X		X		X		X		X		X		X
**Probing depth**				X		X		X		X		X		X		X		X		X		X		X
**Mechanical complication**						X		X		X		X		X		X		X		X		X		X
**Paralleling X-ray**				X				X				X				X				X				X
**Microbiota sample collection**				X		X		X		X		X		X		X		X		X		X		X
**Surface roughness**				X		X		X		X		X		X		X		X		X		X		X

The primary outcomes of the present study are the implant survival rate, peri-implant plaque index (PLI), peri-implant mucosal status, marginal bone resorption rate, and diversity of peri-implant submucosal bacteria species, while the secondary outcomes are the mechanical complication rate and surface roughness measurement.

### Ethical considerations

The proposed study is designed as a prospective, single-center, randomized controlled trial. The study protocol was approved by the Ethics Committee of the Stomatology School and Hospital of Peking University (Beijing, China; approval no. PKUSSIRB-202054027). In addition, the study has been registered with the ClinicalTrials.gov website (https://clinicaltrials.gov/; identifier no. ChiCTR2000029470).

The systematic health status of all study participants will be recorded. Before implant surgery, all patients will be instructed on how to maintain good oral hygiene and undergo clinical and radiographic assessments.

### Recruitment

Patient recruitment was initiated in May 2020. Approximately 50 edentulous patients receive full-arch implant-supported prosthesis every year in this hospital. Announcements were posted in the registration and waiting room areas, and it is expected that 36 eligible participants will be recruited within 2 years. Eligible patients will receive the study protocol and a consent form, which must be completed prior to study inclusion.

Inclusion criteria
Edentulous jawAmerican Society of Anesthesiologists physical status classification of I or IIAge > 22 yearsGood oral hygiene and good complianceSigning of an informed written consent form

Exclusion criteria
Poor oral hygiene and uncontrolled peridontitisAntibiotic use within the past 3 monthsSystemic disease: uncontrolled diabetes mellitus, cardiovascular disease, immunodeficiency disorders, blood disorders such as coagulation disorders, severe osteoporosis, and any metabolic disease that might influence the rate of bone resorptionLong-term medication use: steroid, anti-epileptic drugs, drugs favoring gingival overgrowth, bisphosphonates (bisphosphonate injections or more than 4 years of oral bisphosphonate use), and any medication that influences the rate of bone loss or survival of dental implants, such as selective serotonin re-uptake inhibitors, proton-pump inhibitors, or beta-blockers for the treatment of hypertensionInfection of human immunodeficiency virus, hepatitis B virus, or syphilisBruxismUncontrolled infection in the area intended for implant placement or other areasMaxillofacial tumorFace–neck radiotherapyMental illness or high expectationsUnable to sign the informed consent formSmokers: use of cigarettes, electronic cigarettes, or water pipes

### Interventions

The aim of the treatment protocol is to rehabilitate these patients with full-arch fixed implant-supported prosthesis with placement of 4–6 implants in the mandible. Patients will be randomly assigned to receive one of two restorative materials: zirconia ceramic frameworks with or without ceramic veneering vs. titanium frameworks with acrylic resin veneering. Before prosthesis fitting, the patients will undergo a standard polishing procedure (GB/T 6060.2-2006) and examination to ensure the same surface roughness between groups. The surface roughness of all specimens will be measured with the use of a profilometer (Mitutoyo Surftest SJ-401; Mitutoyo Corporation, Kawasaki, Japan), as described in a previous study [19]. The implant number, implant site, implant diameter, implant length, implant torque, distances between the inserted implants, and shapes of the intaglio surface will be recorded as basic information.

### Primary and secondary outcome variables

The primary outcomes are the implant survival rate, PLI, peri-implant mucosal conditions, marginal bone resorption, and diversity of peri-implant submucosal bacteria species, while the secondary outcomes are the mechanical complication rate and surface roughness of the two treatment groups.

### Clinical assessment

Clinical examinations will be performed at baseline (immediately after prosthesis placement) and every 6 months after implantation of the final prosthesis.

The following parameters will be evaluated: PLI, bleeding index (BI), suppuration (0/1), and probing depth (PD). PLI, suppuration, and PD will be evaluated at four sites per implant (mesiobuccal, buccal, distobuccal, and lingual/palatal) [20]. The PD will be measured to the nearest millimeter using a plastic graded probe (Hu-Friedy Mfg. Co., LLC, Chicago, IL, USA). The BI will be recorded at two sites per implant (buccal and lingual).

The PLI will be assessed as follows: 0, no plaque in the gingival margin area; 1, a thin layer of plaque on the tooth surface of the gingival margin area, but not visible on inspection if the side of the probe tip is used to scrape the plaque; 2, medium amount of plaque on the adjacent surface; or 3, a large amount of soft dirt in the gingival sulcus or the gingival margin area and the adjacent surface.

The BI will be assessed as follows: 0, no inflammation or bleeding on probing; 1, mild marginal inflammation (slight change in color or texture of any portion, but not the entire marginal or papillary gingival unit) and absence of bleeding on probing; 2, mild marginal inflammation (criteria as above but involving the entire marginal or papillary gingival unit) and slight gingival sulcus bleeding on probing; 3, moderate inflammation (glazing, redness, edema, and/or hypertrophy of the marginal or papillary gingival unit) and linear gingival sulcus bleeding on probing; or 4, severe inflammation (marked redness, edema, and/or hypertrophy of the marginal or papillary gingival unit) and bleeding on probing over the sulcus. When recording bleeding, the probing force will be no more than 15 g.

Two examiners will be trained prior to and during the trial to achieve maximum reproducibility of the measurements [21]. For continuous periodontal clinical parameters (PD), the standard error of the measurement will be evaluated. The average level of agreement between the two examiners will be considered satisfactory when greater than 90% (kappa test) for the other clinical variables.

The index developed by Mendez Caramês et al. [22] will be used to evaluate mechanical complications. If no alterations are present, an “alpha” classification will be attributed, and if minor chipping occurs (not requiring any intervention besides polishing or recontouring without the need for prosthesis retrieval), the prosthesis will be recorded as “bravo”; a “Charlie” classification will be attributed to the occurrence of major chipping, need for prosthesis retrieval, and laboratory intervention; and finally, a “delta” classification will indicate a fracture of the framework.

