### X-ray assessment

Marginal bone loss (MBL): immediately after placement of the final prosthesis, a periapical radiograph of each implant will be obtained as well as every year afterward. For standardization, a paralleling technique will be conducted using an intramural digital system (Digora Toto, Soredex, Tuusula, Finland). Kodak Dental Imaging 6.1 software (Carestream Health, Inc., Rochester, NY, USA) will be used for radiographic analysis. The crestal bone level will be measured as the vertical distance between 2 mm below the implant–abutment interface and the most crestal part of the alveolar bone [23, 24]. MBL will be measured mesially and distally for each implant. In each group, peri-implant MBL will be measured to the nearest millimeter.

A peri-implantitis lesion is defined as having PD of ≥ 5 mm with positive suppuration or BI of ≥ 1 and radiographic evidence of bone loss (> 2 mm) or according to consensus [25]. Peri-implant mucositis is defined as being positive for suppuration or BI of ≥ 1 with no radiographic evidence of bone loss. A healthy implant site is defined as a PD of ≤ 4 mm, BI = 0, and no radiographic evidence of bone loss.

The incidences of peri-implantitis and peri-implant mucositis will be determined at 1, 3, and 5 years after final restoration.

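### The bleeding index is scored at two sites per implant while probing depth and suppuration are scored at four, so the combined disease definitions can miss implants whose only positive tissue is mesiobuccal or distobuccal

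*Protocol article*

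**What the plan says.** The Clinical assessment section of the protocol article sets two site schemes. For three measures, "PLI, suppuration, and PD will be evaluated at four sites per implant (mesiobuccal, buccal, distobuccal, and lingual/palatal"). For the bleeding index, "The BI will be recorded at two sites per implant (buccal and lingual").

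The X-ray assessment section adds a third: "MBL will be measured mesially and distally for each implant".

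The same section then combines the measures:

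- "Peri-implant mucositis is defined as being positive for suppuration or BI of" at least 1, without bone loss on the radiograph.
- "A peri-implantitis lesion is defined as having PD of" at least 5 mm, with suppuration or BI of at least 1, and bone loss above 2 mm, "or according to consensus". The content of that consensus is not given.
- A healthy implant site needs probing depth up to 4 mm, BI of 0 and no bone loss.

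A BI of 1, the cut-off in both disease definitions, is mild inflammation of part of the tissue, "but not the entire marginal or papillary gingival unit) and absence of bleeding on probing". The participant timeline (Table 1) lists "Bleeding on probing" at Month 0 and every six months, without a number of sites. Incidence of both conditions is to be determined at 1, 3 and 5 years.

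**The concern.** The definitions join readings taken at different places. BI is absent at two of the four points where probing depth and suppuration are read, and those two points lie nearest the mesial and distal bone readings. Neither section says how the readings are combined across sites.

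Take an implant with a 6 mm mesiobuccal pocket, inflamed tissue there, mesial bone loss above 2 mm, no suppuration, and BI of 0 at the buccal and lingual sites. It fails the numerical peri-implantitis definition because the positive tissue was never scored, and it is not healthy either. An implant with shallow pockets, no bone loss and positive tissue only at an unscored site counts as healthy instead of mucositis.

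Peri-implant mucosal condition is a primary outcome, the biological complication rate is part of the first aim, and the Statistical analysis section compares both disease rates between arms. Readings not taken over five years cannot be recovered by an analysis plan.

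**Working it through.** The protocol states no rate of bleeding, BI positivity or mucositis, so there is no planned figure to reproduce.

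**Step 1: the sites side by side**

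| Measure | Mesiobuccal | Buccal | Distobuccal | Lingual |
|---|---|---|---|---|
| Probing depth, plaque, suppuration | yes | yes | yes | yes |
| BI | no | yes | no | yes |

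Bone level is read mesially and distally only.

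**Step 2: when an implant is lost.** Under an any-site-positive rule, the two BI sites are a subset of the four, so two-site scoring can never flag more implants than four-site scoring. An implant is missed on these signs only if three things hold together: BI is 0 at both scored sites, suppuration is absent at all four sites, and an unscored site would have had a BI of at least 1. For peri-implantitis, the depth and bone criteria must also be met, and the consensus route must not capture the case.

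**Step 3: illustrative size, on assumed values.** Let p be the chance that a site has BI of at least 1, and r the correlation between sites of one implant (exchangeable beta-binomial model). With a = p(1−r)/r and b = (1−p)(1−r)/r, the chance that none of k sites is positive is the product over i = 0,…,k−1 of (b+i)/(a+b+i). At r = 0 it is (1−p)^k, and at r = 1 it is 1−p.

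Worked case, p = 0.1 and r = 0.6: a = 0.0667 and b = 0.6. For two sites, none = 0.900 × 0.960 = 0.864, so any = 13.6%. For four sites, none = 0.864 × 0.975 × 0.982 = 0.827, so any = 17.3%. Two sites find 13.6/17.3 = 79% of what four would flag.

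| p | r | Any of 4 | Any of 2 | Found by 2 |
|---|---|---|---|---|
| 0.1 | 0 | 34.4% | 19.0% | 55% |
| 0.1 | 0.6 | 17.3% | 13.6% | 79% |
| 0.1 | 0.9 | 11.7% | 10.9% | 93% |
| 0.3 | 0 | 76.0% | 51.0% | 67% |
| 0.3 | 0.6 | 46.1% | 38.4% | 83% |
| 0.3 | 0.9 | 33.9% | 32.1% | 95% |
| 0.5 | 0 | 93.8% | 75.0% | 80% |
| 0.5 | 0.6 | 68.2% | 60.0% | 88% |
| 0.5 | 0.9 | 54.6% | 52.5% | 96% |
| any | 1 | p | p | 100% |

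The loss runs from 0% (r = 1) to 45% (p = 0.1, r = 0). At r = 0.6 it is 12% to 21%. Suppuration is not counted here and would reduce it.

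**Step 4: effect on the arm difference, independent sites**

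| p by arm | Two sites | Four sites |
|---|---|---|
| 0.05 vs 0.10 | 19.0 − 9.8 = 9 points | 34.4 − 18.5 = 16 points |
| 0.2 vs 0.4 | 64 − 36 = 28 points | 87 − 59 = 28 points |
| 0.3 vs 0.5 | 75 − 51 = 24 points | 93.8 − 76.0 = 18 points |

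Two-site scoring narrows the contrast when positivity is rare, leaves it unchanged in the middle, and widens it when positivity is common.

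**The case against.** The two-site scheme is stated openly and nothing in the protocol contradicts it, so it is a measurement choice and not an internal error. That stands.

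Four further points narrow what can be claimed:

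- The BI grades describe the gingival margin or papilla as a unit, not a probe point. A buccal score may already reflect tissue toward the corners. The text does not settle this.
- Suppuration is read at all four sites, and peri-implantitis can also be called by the cited consensus. Either route may recover cases.
- A BI of 1 involves no bleeding, so the cut-off raises counts relative to a bleeding-based definition. The net error against true disease is unknown. This does not supply the missing scores.
- The rule is the same in both arms.

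A reader might infer more than the documents support:

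- **That about half of positive implants are missed.** This is the limit for rare, independent signs. The documents give neither prevalence nor correlation.
- **That the arm difference is diluted.** Step 4 shows that this depends on prevalence.
- **That bleeding at the unscored sites is seen and simply not written down.** The 15 g limit is stated for recording bleeding, and no force is given for probing depth, so a single pass serving both is an assumption.
- **That health cannot be judged at half the sites.** The Interventions section lists implant site among per-implant characteristics. On that reading the healthy definition applies to the implant, and no BI is missing.

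**Conclusion.** The mismatch is certain: four sites for probing depth and suppuration, two for BI, within definitions that use them together. Its consequence is a possible loss of cases, not a demonstrated one. Relative to four-site BI scoring under an any-site rule, the count is equal or lower. The shortfall in BI-positive implants is unknown, and runs from none to about 45% for assumed site prevalence of 0.1 to 0.5 and correlation of 0 to 1, before suppuration and the consensus route. The large end needs independence between sites around one implant, which is the extreme case. No differential bias between arms is shown. The point is worth acting on because the outcome is primary, the readings cannot be recovered later, and four-site scoring gives more complete ascertainment and a more precise BI at little cost.

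**What to change.** In the Clinical assessment section, record BI at the same four sites as plaque, suppuration and probing depth. In the X-ray assessment section, state that the definitions apply at implant level, with any site positive counting. Do not require depth, BI and bone loss to match at the same aspect: that would tighten the peri-implantitis definition and leave the mid-buccal and lingual sites without a bone reading.

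The cost is two more BI scores per implant per visit, or 8 to 12 per patient with 4 to 6 implants, taken within the 15 g limit stated for bleeding. The any-positive rate will be equal or higher, and for mucositis it could approach a ceiling if a BI of 1 is common. The buccal and lingual scores remain in the data, so the two-site result can still be reported alongside, including for any visits completed before the change.

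### The bleeding index ties each level of visible inflammation to one bleeding state, so some non-bleeding implants count as mucositis and implants that bleed without visible change have no grade

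*Protocol article*

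**What the plan says.** The scale is set out in the protocol article under Clinical assessment and is scored at two sites per implant:

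- Grade 0: "0, no inflammation or bleeding on probing".
- Grade 1: mild inflammation, described as "slight change in color or texture of any portion, but not the entire marginal or papillary gingival unit", with bleeding excluded. The text runs on into grade 2 as "and absence of bleeding on probing; 2, mild marginal inflammation".
- Grade 2: "criteria as above but involving the entire marginal or papillary gingival unit) and slight gingival sulcus bleeding on probing".
- Grade 3: moderate inflammation "and linear gingival sulcus bleeding on probing".
- Grade 4: severe inflammation "and bleeding on probing over the sulcus".

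The case definitions are under X-ray assessment. The first reads "Peri-implant mucositis is defined as being positive for suppuration or BI of" 1 or more, without bone loss on the radiograph. Peri-implantitis needs a probing depth (PD) of at least 5 mm, suppuration or BI ≥ 1, and bone loss above 2 mm, with a consensus definition as an alternative. A healthy site needs PD of 4 mm or less, BI = 0 and no bone loss.

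Table 1 schedules the assessment as "Bleeding on probing". Peri-implant mucosal condition is a primary outcome (Primary and secondary outcome variables). Mucositis and peri-implantitis incidence is determined at 1, 3 and 5 years. The Statistical analysis section compares these rates by chi-square test and also compares BI between groups and over the 10 follow-ups.

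**The concern.** Three parts of the article describe the same measurement differently. The schedule names bleeding. The scale grades visible inflammation and bleeding together. The case definitions cut that scale at a point where bleeding is absent by definition. A reader of the results could take the mucositis rate as a rate of bleeding implants, and it would not be one.

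The scale also assumes that the two signs always rise together. Where they do not, the examiner has no grade to give, and the article states no rule for such sites. One of these gaps lies at the cut between BI = 0 and BI ≥ 1, which decides whether an implant is healthy or a mucositis case. At stake are the meaning and repeatability of the mucositis rate, and noise in the BI comparison itself.

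**Working it through.** The article gives no figure to reproduce here, so the check sets the definitions side by side and counts the combinations.

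**Step 1: grades and case status.** Take an implant with no suppuration and no bone loss.

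| BI | Visible change | Bleeding | Status |
|---|---|---|---|
| 0 | none | none | healthy if PD ≤ 4 mm |
| 1 | mild, part of the unit | none | mucositis |
| 2 | mild, whole unit | slight | mucositis |
| 3 | moderate | linear | mucositis |
| 4 | severe | over the sulcus | mucositis |

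One of the four grades that meet BI ≥ 1 is defined by the absence of bleeding.

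**Step 2: combinations with a grade.** The scale names 5 levels of visible change and 4 bleeding states: 5 × 4 = 20 combinations. Five have a grade, and 20 − 5 = 15 do not. With bleeding reduced to yes or no there are 5 × 2 = 10 combinations, of which 5 have a grade and 5 do not.

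**Step 3: which of those five can change case status.**

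- *No visible change, bleeding.* Grade 0 fails on bleeding. Grade 1 fails on both signs. Grade 2 fails on visible change. Grades 0 and 2 each break one condition and lie on opposite sides of the cut, so the status is open.
- *Partial mild change, bleeding.* The nearest grades are 1 and 2, and both make it a case. Only the BI value is uncertain.
- *Whole-unit mild change, no bleeding.* Again 1 or 2, and a case either way.
- *Moderate change, no bleeding*, and *severe change, no bleeding.* Visible inflammation rules out grade 0, so each is a case whatever grade is chosen.

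So 1 of the 5 can move an implant between healthy and mucositis. The other 4 affect the BI comparison only. If grade 0 is read as allowing bleeding when inflammation is absent, the first combination becomes healthy despite bleeding, which does not remove the conflict with the label in Table 1.

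**Step 4: does the choice of sign matter, and in which direction?** The article gives no distribution of BI grades, so the following values are assumptions and not estimates. Let p be the share of implants that bleed and g the share of non-bleeding implants graded 1. A bleeding definition gives p; BI ≥ 1 gives p + (1 − p)g.

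- p = 0.40 vs 0.20, g equal in both arms. At g = 0.1: 0.40 + 0.60 × 0.1 = 0.46 vs 0.20 + 0.80 × 0.1 = 0.28. At g = 0.2: 0.52 vs 0.36. At g = 0.3: 0.58 vs 0.44. The 20-point gap becomes 18, 16 or 14 points.
- Same p, g = 0.3 vs 0.1: 0.58 vs 0.28, a gap of 30 points.
- p = 0.20 in both arms, g = 0.2 vs 0.1: 0.36 vs 0.28, a gap of 8 points where the bleeding definition shows none.

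The two definitions can give different answers, and the direction depends on values that the article does not supply.

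**The case against.** The strongest reply is that nothing in the article says disease must mean bleeding. Grade 1 is itself described as inflammation, the primary outcome is mucosal condition, and health requires BI = 0. Counting visible inflammation as mucositis is consistent with that, and the Table 1 row may be no more than a short label. This stands. A reader might infer that every grade 1 implant is a false positive, but the documents do not support that. What remains is that the label, the scale and the cut do not tell the reader which sign defines a case.

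Second, most of the ungraded combinations do not alter the disease count. This also stands, as Step 3 shows: only bleeding without visible change can. A reader might infer general misclassification in both directions, which goes too far.

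Third, peri-implantitis cannot rest on BI alone, because probing depth and bone loss must also be met. This stands and places the direct effect on mucositis. The consensus alternative is attached to peri-implantitis only, so it does not settle the mucositis definition.

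Fourth, examiners are trained, with an agreement target above 90%; a manual may hold rules for mixed findings; and a bleeding-only cut at BI ≥ 2 could be derived later. This stands in part. Training can make two examiners agree on a convention, but the printed scale still has no grade for these sites. The later cut works only where the two signs agree: a bleeding site recorded as 1, or a non-bleeding site recorded as 2, cannot be recognised from the grade.

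**Conclusion.** The point holds in limited form. As printed, a non-bleeding implant with slight partial change and no bone loss is a mucositis case. An implant that bleeds without visible change has no grade, although its status depends on the grade given. The other discordant findings add noise to the BI comparison. The direct effect is on the mucositis rate, which belongs to a primary outcome; for peri-implantitis the issue arises only in implants that also meet the PD and bone-loss criteria.

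The size cannot be computed without a distribution of BI grades. A reader might infer that the scale dilutes the difference between the arms or biases it towards one material. The documents establish neither: the assumed values in Step 4 give a narrower gap, a wider gap or a gap from nothing, depending on how grade 1 is spread over the arms. The conclusion rests on reading each grade as requiring both of its signs, as the wording does, and on the article stating no rule for discordant sites. It takes no view on which clinical definition is right.

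**What to change.** 1. At each BI site, record two fields: bleeding on probing (none, slight, linear, over the sulcus) and visible inflammation (the five levels the scale already uses). The combined grade can still be derived where the signs agree.
2. Reconcile Table 1, Clinical assessment and X-ray assessment by stating whether the case definitions rest on bleeding, on visible inflammation or on either.
3. Make the healthy, mucositis and peri-implantitis definitions consistent with that choice, so that no site falls between healthy and mucositis on this criterion. Moving the cut to BI ≥ 2 alone would not do this: a grade 1 site without suppuration or bone loss would then be neither, because health requires BI = 0.
4. Report the mucositis comparison under the other definition as a sensitivity analysis.

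The cost is a slightly longer case report form and some added examiner training. No procedure is added, because both signs are already observed. The change is best made early, since visits recorded only as a combined grade cannot be fully separated afterwards.
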